#### 7.1.2 Secondary endpoints

Time to progression is defined as the number of days from randomization to the first occurrence of the respective event.

#### Fatigue

Fatigue will be assessed additionally at time points 5 weeks, 6 months, 2 years, 5 years after treatment start.

#### Local tumor control in the index quadrant of the breast

Local tumor control in the index quadrant of the ipsilateral breast as a secondary endpoint is defined as no tumor relapse in the breast tissue quadrant of the initial tumor/ at the site of surgical intervention. Local tumor control in the index quadrant of the ipsilateral breast is used as an additional secondary endpoint to distinguish between true local recurrences in the index quadrant from second (or new) ipsilateral carcinomas in other quadrants. In the intraoperative study arm (arm B) only the former tumor bed is irradiated, while in study arm A the whole breast tissue is irradiated.

Local tumor control in the index quadrant of the breast is taken as number of days from randomization until local tumor progression, death without prior local progression, or end of follow-up. For patients alive and not diagnosed with local progression at the end of the study, the local control time will be censored at the time of the last study visit.

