## **1.2 Trial Rationale/ Justification**

The primary goal of this trial is to show that BCS followed by APBI with electrons results in a significantly better tolerability of adjuvant radiotherapy in terms of fatigue compared to BCS followed by hypofractionated WBRT. Fatigue is a major side effect of cancer treatments and is a main contributor to long-term quality of life-impairment as well as unemployment. The prognosis of women with early stage, low risk breast cancer is excellent and the risk of local recurrence after BCS has been shown to be in the range of 1-2% at 5 years after diagnosis. Thus, maintaining a high quality of life and minimizing morbidity and mortality of adjuvant treatment is crucial.

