#### **Local tumor control in the ipsilateral breast**

Local tumor control in the ipsilateral breast as a secondary endpoint is defined as no tumor relapse in the whole ipsilateral breast tissue. Local tumor control in the ipsilateral breast is taken as number of days from randomization until local tumor progression, death without prior local progression, or end of follow-up. For patients alive and not diagnosed with local progression at the end of the study, the local control time will be censored at the time of the last study visit.

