#### **Regional tumor control**

Regional tumor control is regarded as no occurrence of regional lymph node metastases (axilla, supraclavicular fossa, internal mammary chain). Regional tumor control is defined as number of days from randomization until occurrence of regional lymph node metastases, death without prior regional tumor progression, or end of follow-up. For patients alive and not diagnosed with regional progression at the end of the study, the regional tumor control time will be censored at the time of the last study visit.

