#### **Distant tumor control**

Distant tumor control is defined as no occurrence of distant metastases (lymph node metastases in the axilla, supraclavicular fossa and internal mammary chain are not classified as distant metastases, see above). Distant tumor control is defined as number of days from randomization until occurrence of distant metastases, death without prior distant progression, or end of follow-up. For patients alive and not diagnosed with distant progression at the end of the study, the distant tumor control time will be censored at the time of the last study visit.

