### 10.2.3 Further analyses

In addition to the evaluation of the FAS, a PP analysis will be performed as a sensitivity analysis. The secondary outcomes will be analyzed descriptively by tabulation of the measures of the empirical distributions. According to the scale level of the variables, means, standard deviations, medians, 1st and 3rd quartiles as well as minimum and maximum or absolute and relative frequencies, respectively, will be reported. Further, for the secondary endpoints overall survival (OS), disease-free survival (DFS), local, regional, and distant tumor control, a Kaplan-Meier analysis will be performed and a between-groups comparison via a descriptive log-rank test will be conducted. Adverse and Serious Adverse Events will be tabulated and absolute and relative frequencies with 95% confidence intervals will be calculated. The severity and the relationship to the treatment will be given. Possible differences between the treatment groups will be tested using the chi-squared test. Descriptive p-values of the corresponding statistical tests comparing the treatment groups and associated 95% confidence intervals will be given. Further exploratory analyses will be performed to identify subgroups and potential moderator variables of patients profiting distinctly from the investigated interventions. Analyses will be conducted using SAS v9.4 (SAS Institute, Cary, NC)

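### Local, regional and distant tumor control are described as freedom from relapse, but their time variables also end at death, so Kaplan-Meier would estimate a relapse-or-death composite under the name of tumor control

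*Protocol*

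**What the plan says.** Protocol section 7.1.2 gives each of the four control endpoints two descriptions.

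- **In words.** Index-quadrant control "is defined as no tumor relapse in the breast tissue quadrant of the initial tumor" (or surgical site). Control in the ipsilateral breast "is defined as no tumor relapse in the whole ipsilateral breast tissue". Regional and distant control are likewise the absence of nodal or distant metastases. Death is not mentioned.
- **As a time variable.** Index-quadrant control "is taken as number of days from randomization until local tumor progression, death without prior local progression, or end of follow-up", and the ipsilateral-breast endpoint has the same construction. Regional control runs "until occurrence of regional lymph node metastases, death without prior regional tumor progression, or end of follow-up" and distant control "until occurrence of distant metastases, death without prior distant progression, or end of follow-up".

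The censoring rule for local control is: "For patients alive and not diagnosed with local progression at the end of the study, the local control time will be censored". The regional and distant endpoints have the matching rule. No rule censors a patient who dies without relapse.

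For OS, DFS and all the control endpoints, section 10.2.3 states that "a Kaplan-Meier analysis will be performed and a between-groups comparison via a descriptive log-rank test will be conducted". It names no competing-risk method. Section 2.2 sets the reporting times for control at 2 and 5 years. Section 1.2 says that in this population the "risk of local recurrence after BCS has been shown to be in the range of 1-2% at 5 years". The protocol states no expected mortality and no expected regional or distant rate.

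**The concern.** The verbal definition and the time variable measure different things. The first is freedom from relapse at a site. The second, read with its censoring rule, is survival free of relapse at that site. A Kaplan-Meier curve of the second is a valid estimate of a composite; the fault is that it would be reported as tumor control.

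Three consequences follow.

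- The reported control percentages would be lower than the proportion free of relapse.
- A difference between arms in relapse would be diluted by deaths common to both.
- An imbalance in deaths between arms could be read as a difference in control. Section 1.1 itself reports significantly fewer deaths from causes other than breast cancer in the intraoperative arm of one cited trial.

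These endpoints are the protocol's site-specific comparison of tumor control after intraoperative electrons and whole-breast irradiation. The composite that includes death is already covered by DFS.

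**Working it through.** **Which reading the text supports.** A patient who dies without local relapse reaches a listed end of the time variable and does not meet the censoring condition, which requires being alive. That leaves an event. DFS, in the same section, also lists death without progression as an end point and again censors only living patients.

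**Inputs.**
- N = 202 (sections 5.1 and 10.1). The figure is consistent with the plan: 86 per group gives power 0.903 for 6 points with SD 12, and 172/0.85 = 202.35.
- r = 5-year local recurrence risk, 1-2% (section 1.2). It is not split by quadrant. Index-quadrant relapses can only be as many or fewer.
- d = 5-year risk of death without prior local relapse. **This is not in the protocol**; the assumed range is 1-8%.
- Constant competing hazards and complete 5-year follow-up are assumed.

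**Formulas.** Share of failures that are deaths = ln(1−d) / [ln(1−d) + ln(1−r)]. Reported local control = (1−r)(1−d). Counted failures = 202 × [1 − (1−r)(1−d)].

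**One cell in full** (r = 2%, d = 3%):
- −ln 0.97 = 0.0305 and −ln 0.98 = 0.0202, so the share is 0.0305/0.0507 = 60%.
- Control = 0.98 × 0.97 = 95.1%.
- Failures = 202 × 0.0494 = 10.0, of which 6 are deaths and 4 are relapses.

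| Assumed d | Death share, r = 1% | Death share, r = 2% | Reported control, r = 1% / 2% |
|---|---|---|---|
| 1% | 50% | 33% | 98.0% / 97.0% |
| 2% | 67% | 50% | 97.0% / 96.0% |
| 3% | 75% | 60% | 96.0% / 95.1% |
| 5% | 84% | 72% | 94.0% / 93.1% |
| 8% | 89% | 80% | 91.1% / 90.2% |

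Counting relapse only, 202 × 1% ≈ 2 and 202 × 2% ≈ 4 events, and 98-99% are relapse-free. At d = 3-8% the composite has about 8 to 20 events. Deaths are the majority exactly when d exceeds r.

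**Dilution, as an illustration.** Section 1.1 quotes 5-year local recurrence of 0.4% after WBI and, with higher-risk patients excluded from the intraoperative arm, 1.5% after IORT.
- Relapse only: hazard ratio = ln 0.985 / ln 0.996 = 0.01511/0.00401 = 3.8.
- Composite, d = 3% in each arm: (0.01511 + 0.03046)/(0.00401 + 0.03046) = 1.3.
- Composite, d = 5%: (0.01511 + 0.05129)/(0.00401 + 0.05129) = 1.2.

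**If deaths were censored instead.** Suppose 2% relapse first and 5% die first. The cumulative relapse hazard is (2/7) × (−ln 0.93) = 0.02073, so 1 − Kaplan-Meier = 2.05%. With 8% deaths it is (2/10) × (−ln 0.90) = 0.02107, giving 2.09%. The overstatement is below 0.1 percentage point.

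**The case against.** The strongest reply is that the list of end points also contains the end of follow-up, which is plainly a censoring. The list may therefore name the ways observation stops, not the events. The opening of section 7.1.2 does count time to the respective event. On that reading deaths are censored, the bias is under 0.1 percentage point, and the planned log-rank is already the cause-specific test. The size of that bias stands, so censoring deaths would do little harm. The reading itself does not fit the censoring rule, which is confined to living patients.

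A second reply is that section 10.2.3 tabulates secondary outcomes and reports OS and DFS alongside, so relapse counts and an imbalance in deaths would be visible. That helps a careful reader but does not correct the Kaplan-Meier figures labelled as control.

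A third concerns the index-quadrant endpoint, which is meant to separate true recurrences from new tumors elsewhere in the breast. The same deaths enter both local endpoints and largely cancel when the two are compared, so it would be too much to say that this contrast is lost.

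Finally, the endpoints are secondary, the log-rank is descriptive, and 2-4 local relapses could not settle comparative tumor control under any analysis. This stands and limits the weight of the point.

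**Conclusion.** The inconsistency is real and should be corrected, but it is not critical to the trial. As written, all four endpoints are site-specific relapse-or-death composites carrying the name of tumor control.

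A reader might infer that most counted failures would be unrelated deaths. The documents do not support that in general:
- The protocol gives no mortality. For local control, deaths are the majority only if the 5-year death risk exceeds the recurrence risk. This holds throughout an assumed 3-8% (share 60-89%) but not at 1% (33-50%).
- No share can be computed for regional or distant control.
- Such deaths need not be unrelated, because a death from distant breast cancer without local relapse would also count as a local failure.

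The direction is certain for any deaths at all: reported control falls below the relapse-free proportion. The size depends on the assumed mortality. The primary fatigue analysis and the 202 patients are unaffected.

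**What to change.** - **Section 7.1.2:** for each control endpoint, make relapse or metastasis at the named site the only event. State that death without it is a competing event. Keep censoring for patients alive and free of that event.
- **Section 10.2.3:** for the four control endpoints, report cumulative incidence (Aalen-Johansen) at 2 and 5 years with 95% CI by arm. Add a descriptive cause-specific log-rank test (deaths censored) or Gray's test. Keep Kaplan-Meier for OS and DFS, where death belongs in the endpoint.
- **Optional:** state how ipsilateral relapse outside the index quadrant is handled in the index-quadrant endpoint. This is a choice of estimand, not an error to repair.

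The cost is wording in these two sections. No new data, visits or patients are needed.

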#### **Local tumor control in the ipsilateral breast**

Local tumor control in the ipsilateral breast as a secondary endpoint is defined as no tumor relapse in the whole ipsilateral breast tissue. Local tumor control in the ipsilateral breast is taken as number of days from randomization until local tumor progression, death without prior local progression, or end of follow-up. For patients alive and not diagnosed with local progression at the end of the study, the local control time will be censored at the time of the last study visit.

#### **Regional tumor control**

Regional tumor control is regarded as no occurrence of regional lymph node metastases (axilla, supraclavicular fossa, internal mammary chain). Regional tumor control is defined as number of days from randomization until occurrence of regional lymph node metastases, death without prior regional tumor progression, or end of follow-up. For patients alive and not diagnosed with regional progression at the end of the study, the regional tumor control time will be censored at the time of the last study visit.

#### **Distant tumor control**

Distant tumor control is defined as no occurrence of distant metastases (lymph node metastases in the axilla, supraclavicular fossa and internal mammary chain are not classified as distant metastases, see above). Distant tumor control is defined as number of days from randomization until occurrence of distant metastases, death without prior distant progression, or end of follow-up. For patients alive and not diagnosed with distant progression at the end of the study, the distant tumor control time will be censored at the time of the last study visit.

#### **Overall survival**

Overall survival time, defined as number of days from randomization until death or end of follow-up. For patients alive at the end of the study, the overall survival time will be censored at the time of the last visit or follow-up contact.

#### **Disease-free survival**

Disease-free survival, defined as number of days from randomization until the first occurrence of local recurrence, regional lymph node metastases, distant metastases, tumor-related death, death without prior progression, or end of follow-up. For patients alive and not diagnosed with progression at the end of the study, the disease-free survival time will be censored at the time the patient was last known to be free of progression of tumor disease.

## Secondary malignancies

The frequency of secondary malignancies as well as the time of their diagnosis will be assessed during follow-up visits.

## Toxicity/ quality of life

Detailed acute and chronic potentially therapy-related toxicity will be assessed during each follow-up visit and documentation of side-effects with Common Terminology Criteria for Adverse Events and with the Radiation Therapy Oncology Group (RTOG)/ European Organization for Research and Treatment of Cancer (EORTC) Late Radiation Morbidity Scoring System Schema. Documentation of toxicity will mainly focus on breast shrinkage/distortion, breast induration/fibrosis, change of skin appearance, telangiectasia, breast oedema, numbness, fat necrosis and local pain. QoL will be analyzed with the help of the validated 30-item self-assessment questionnaire of the European Organization for Research and Treatment of Cancer (EORTC QLQ-C30, version 3.0). It is composed of five multi-item functional scales (physical, role, emotional, cognitive, and social function), three multi-item symptom scales (fatigue, pain, nausea/vomiting) combined with a global health and quality-of life scale. The other six single items assess further symptoms (dyspnea, insomnia, appetite loss, constipation, diarrhea) that are often reported by cancer patients as well as financial difficulties. Scores are interpreted according to the guidelines of the EORTC Scoring Manual.

The BREAST-Q questionnaire is a validated survey instrument especially developed for patients undergoing breast surgery. An extra BREAST-Q BCS module exists, which is specifically designed for patients undergoing BCS measuring quality-of-life (QOL) and satisfaction. Both of these topics are divided into three subscales i.e., QOL: physical, psychosocial and sexual well-being; Satisfaction: satisfaction with cosmetic outcome (breast appearance), satisfaction with overall outcome and satisfaction with care. Patients are asked to rate each item question on a four-point scale. The BREAST-Q is separated into a pre- and post-surgery version.

The Breast Cancer Treatment outcome scale (BCTOS-12) contains 12 items, which are assigned to two internally consistent subscales: 1) Functional Status, 2) Aesthetic Status. Patients are instructed to rate each item of the BCTOS-12 on a four-point scale evaluating the differences between the treated and the untreated breast (1 = no difference, 4 = large difference). The score for each subscale is the mean of the ratings over all items belonging to that subscale. A higher score reflects a poorer status (i.e. a larger difference between the treated and the untreated breast).

**Patient Administration time:** 15-20 minutes

### 7.1.3 Explorative Endpoint

#### **Gene expression analysis using the Prosigna/PAM50-assay**

The Prosigna/PAM50-assay will be applied on the operatively resected tumor tissue according to manufacturer's instructions.

## **8. Plan for Treatment or Care after the Trial**

After completion of study treatment, any standard treatment may be considered. Any systemic treatment or chemotherapy is not part of the clinical trial. For tumor progression, treatment alternatives will be evaluated and discussed interdisciplinary considering options of surgical resection, systemic therapy (chemotherapy, molecular targeted therapies, immunotherapy) as well as re-irradiation in certain cases.

## **9. Assessment of Safety**

During and following a subject's participation in the trial, the investigator should ensure that adequate medical care is provided to a subject for any adverse. The investigator should inform a subject when medical care is needed for intercurrent illness(es) of which the investigator becomes aware. RT will be carried out as ambulatory treatment; however admission to the ward for supportive care is possible when necessary. Supportive measures include skin care, pain management will be performed at the discretion of the treating radiation oncologist.

### **9.1 Adverse Events**

Toxicity associated to irradiation that occurs for the first time after treatment start or preexisting toxicity that significantly increases in the severity grade after the start of study treatment likely to be related to radiotherapy will be documented within the subject's medical records and eCRF. Treatment related side effects will be recorded according to CTCAE v5.0 (Common Terminology Criteria for Adverse Events version 5.0; <http://www.eortc.be/services/doc/ctc>). Grades refer to the severity of the adverse event.

Acute toxicities are defined by the occurrence within the first 90 days after the start of RT. Adverse Events occurring after the first 90 days until 6 months after study treatment will be documented as subacute toxicities. Any adverse event emerging more than 6 months after RT will be recorded as late toxicities.

Standardized informed consent forms for irradiation of breast cancers are utilized to inform the patient about study treatment. Expected acute side effects of RT include radiation dermatitis, fatigue, pain, soreness and dryness of the breast, pruritus of the skin, hairloss in the axilla, sore

throat and change in breast size, shape and color. Characteristics and severity of subacute/ late side effects depend on the location and the extent of the target volume/ irradiation field and include skin fibrosis, change in breast size, shape and color, lymphoedema, lung fibrosis, rib fractures, cardiac disorders like cardiac arrhythmia, cardiac insufficiency and coronary heart disease, soft tissue necrosis as well as brachial plexopathy.

Acute/ subacute toxicities will be assessed prior, during and after RT, including:

- Skin disorders: radiation dermatitis, dryness and pruritus of the skin, hairloss in the axilla, lymphedema
- Breast disorders: pain, swelling, change in breast size, shape and color
- Endocrine disorders: hot flashes, night sweats, bone pain
- Lung disorders: coughing, dyspnea
- Gastrointestinal disorders: nausea and vomiting
- Other disorders: alopecia, weight loss

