## **5.6 Prior and Concomitant Illnesses**

Relevant additional illnesses present at the time of informed consent are regarded as concomitant illnesses and will be documented in the patient chart. Abnormalities which appear for the first time or worsen (intensity, frequency) during the trial are adverse events (AEs) and must be documented on the appropriate pages of the CRF.

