## **9.2 Serious Adverse Events**

A serious adverse event is an adverse event with a special degree of severity in that it

- leads to death (CTCAE grade 5)
- is life-threatening (CTCAE grade 4) due to its actual and documented severity at the point of occurrence (not only life-threatening in principle if occurrence was more severe)
- causes or prolongs hospitalization
- is a congenital anomaly/ birth defect
- leads to a lasting or otherwise significant impairment
- is an otherwise significant medical incident

The following examples are not to be considered SAE:

- Medical or surgical interventions
- Hospital admissions that are not the consequence of a medical condition (e. g. social/ convenience admissions)
- day-to-day fluctuations of pre-existing illness(es) or toxicity present or detected at the start of the study that do not worsen
- A planned hospitalization where admission did not take longer than anticipated
- Tumor progression and all medical intervention performed to offer respective therapy or relieve the symptoms of such progression

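### Sections 5.6, 7.1.2 and 9.1 give conflicting rules for recording adverse events, and the 9.1 rule would act unequally on the two arms until whole breast irradiation starts

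*Protocol*

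**What the plan says.** Three sections of the protocol state what is to be recorded.

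- **Section 5.6:** "Abnormalities which appear for the first time or worsen (intensity, frequency) during the trial are adverse events (AEs) and must be documented". The CRF is the place of record, and there is no condition on cause.
- **Section 9.1:** two categories go into the medical records and eCRF. The first is "Toxicity associated to irradiation that occurs for the first time after treatment start". The second is "preexisting toxicity that significantly increases in the severity grade after the start of study treatment likely to be related to radiotherapy will be documented". Both carry a link to radiation. The section then says that treatment-related side effects are graded by CTCAE.
- **Section 7.1.2 (Toxicity/quality of life):** toxicity that may be related to therapy is assessed at each follow-up visit, with CTCAE and the RTOG/EORTC late scale.

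Two later sections build on whichever rule applies. Section 9.2 states: "A serious adverse event is an adverse event with a special degree of severity in that it", followed by the usual seriousness criteria and no condition on relatedness. Section 10.2.3 tabulates AEs and SAEs and adds: "The severity and the relationship to the treatment will be given. Possible differences between the treatment groups will be tested using the chi-squared test".

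On timing, the synopsis equates treatment start with surgery. Section 6.4 places whole breast irradiation in arm A at 5 (± 2) weeks after surgery and the T1 visit just before it. Arm B is irradiated at surgery. T1 includes an AE assessment in both arms.

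**The concern.** A site cannot follow three thresholds at once, and the internal monitoring in section 11.2, which reviews AE and SAE notification, has no single standard to check against. This is a collection rule, so it cannot be left to the analysis: an event that was never entered in the eCRF cannot be recovered later.

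The choice also matters for the comparison of arms. A rule that depends on attribution to radiotherapy acts differently in an arm that has been irradiated and an arm that has not. For about the first five weeks, arm A is not yet irradiated and arm B is. Acute toxicity is a named secondary endpoint, and better tolerability is part of the trial's rationale, so an artefact here would fall on a result that readers will look for.

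**Working it through.** The protocol states no AE rate and no power for safety, so there is no figure to reproduce. The check compares the texts, follows the timeline and then gives an illustration.

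**1. The rules side by side**

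| Section | What is recorded or assessed | Condition on cause |
|---|---|---|
| 5.6 | any new or worsening abnormality during the trial | none |
| 7.1.2 | toxicity at each follow-up visit | possibly related to therapy |
| 9.1 | new or worsened toxicity | associated with irradiation, or likely related to radiotherapy |

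Take postoperative breast swelling that the physician ascribes to surgery. It must be documented under 5.6, it arguably counts under 7.1.2 (surgery is part of therapy), and it does not meet 9.1.

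**2. The timeline**

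- Arm A: surgery at week 0, T1 at about week 5 before radiotherapy, whole breast irradiation from week 5 (range 3 to 7).
- Arm B: surgery and irradiation at week 0, T1 five weeks after irradiation.
- The work-flow table in section 6.4 schedules AE documentation at T1 and T2 only. On the stated schedule, one of these two visits precedes any radiotherapy in arm A. The windows overlap, so T1 may fall after the start of irradiation in some women.

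Under 9.1, therefore, an arm A event before irradiation has nothing to be attributed to. The same event in arm B can be attributed to the intraoperative dose. The distortion in this window can only raise arm B's recorded count relative to arm A's.

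**3. What the later sections need**

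Reporting the relationship to treatment (10.2.3) is informative only if unrelated events are collected too, which fits 5.6. An SAE (9.2) is a subset of AEs and takes on whichever AE rule is used.

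**4. Illustration on assumed rates**

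The 202 randomised patients at 1:1 give 101 per arm (no dropout). Let *e* be the true risk of an early event (before irradiation in arm A), *l* the true risk of a later event, both equal in the two arms and independent, and *a* the share of arm B's early events attributed to radiotherapy. Later events are taken as recorded in both arms. Under 9.1:

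- recorded proportion in arm A = *l*
- recorded proportion in arm B = 1 − (1 − *l*)(1 − *e·a*)

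For *l* = 20%, *e* = 20%, *a* = 50%: arm A 20%; arm B 1 − 0.8 × 0.9 = 28%. The probability that the 5% Pearson chi-squared test rejects, by full binomial enumeration with *l* = 20%, is:

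| *e* | *a* = 25% | *a* = 50% | *a* = 100% | all events recorded |
|---|---|---|---|---|
| 10% | 6.5% | 10.6% | 26.4% | 5.0% |
| 20% | 10.6% | 26.4% | 72.3% | 4.9% |
| 30% | 17.3% | 49.5% | 96.1% | 5.5% |

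For an event type confined to the early window (*l* = 0), arm A records none. With *k* of 101 recorded in arm B, Pearson's statistic reduces to 202*k*/(202 − *k*). If 20 of 101 women in each arm truly have such an event and 25%, 50% or 100% are attributed in arm B:

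- *k* = 5: 1010/197 = 5.13, p = 0.024
- *k* = 10: 2020/192 = 10.52, p = 0.0012
- *k* = 20: 4040/182 = 22.2, p < 0.0001

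The first of these is fragile. The expected counts are 2.5 per arm, and Fisher's exact test gives p of about 0.06.

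**The case against.** The best defence is that the sections can be read together. Section 5.6 defines an AE and makes documentation mandatory; 9.1 then only adds grading and the acute, subacute and late classes for radiation toxicity. Section 9.1 does not contain the word only. It also has toxicities assessed before, during and after radiotherapy and lists items such as hot flashes and weight loss. T1 assesses AEs in both arms, and 7.1.2 offers a wider route for the toxicity endpoint. This reading is possible. But 9.1 is the section headed Adverse Events, and its documentation sentence carries a radiation link that 5.6 lacks. The text does not say which rule prevails.

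Several stronger readings are tempting, and the documents do not support them.

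- **Relatedness is judged by an unblinded investigator.** The protocol describes concealed allocation, mentions no blinding and does not say who judges relatedness. Lack of blinding is plausible given the treatments, but it is an inference.
- **Unrelated serious events are excluded from the SAE tables.** Section 9.2 has no relatedness condition and can be read with 5.6. The loss arises only if it is read with 9.1.
- **Arm A's events before irradiation can never be recorded.** This holds under 9.1 alone; 5.6, 7.1.2 and the T1 assessment give them another route.
- **A signal in non-breast-cancer deaths would be lost.** All deaths count in overall survival and in disease-free survival unless a disease event came first. Secondary malignancies are a separate endpoint. None of these passes through 9.1.
- **The termination triggers in 5.5.5 are corrupted.** They are written for graded toxicities, so resting on toxicity data is their stated design.

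The illustration is also open to challenge. Its rates are assumed, its lowest result (6.5%) is close to nominal, and the plan contains no test restricted to the early window.

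**Conclusion.** The conflict stands. Sections 5.6, 7.1.2 and 9.1 set three thresholds for the same data. If 9.1 is the one applied, the descriptive between-arm AE comparison in 10.2.3 could be biased against arm B in the weeks before arm A starts irradiation, and non-fatal SAEs judged unrelated could go unrecorded if 9.2 is read with 9.1.

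The direction in that window follows from the schedule. The size does not: it depends on the early event rate and on the share attributed to the intraoperative dose, neither of which the protocol gives. Over the assumed ranges, false rejection runs from near nominal (6.5%) to 96%, so the effect may be trivial or large.

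The AE tests are secondary and descriptive, deaths have their own endpoints, and the primary fatigue analysis is untouched. This should be fixed, since uncollected events cannot be restored, but it does not threaten the trial's main conclusion.

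**What to change.** Reconcile sections 5.6, 7.1.2, 9.1, 9.2 and 10.2.3 around one rule:

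- Use the 5.6 definition in 9.1: record every new or worsening event from surgery (treatment start) onward in both arms, whatever its cause.
- Hold relationship as a separate eCRF field, distinguishing radiotherapy from surgery.
- State that 9.2 applies to all recorded AEs.
- In 10.2.3, compare all-cause events between arms first, with related events as a supporting table.
- Keep the CTCAE grading and the acute, subacute and late classes as descriptions of recorded events, not as conditions for recording them.

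Moving the start of the acute window to surgery would not be enough on its own, because the attribution condition would still act unequally.

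The cost is protocol wording, one eCRF field and somewhat more AE entries. No extra visits are needed.
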